# Aims

The aim of this study is a ‘proof-of-concept’, i.e. to determine whether a comprehensive

intervention is feasible and results in improvement in both angina and CMD.

The study is a pilot study which we, if successful, will seek to expand to a multicenter interventional trial with prognostic outcome in collaboration with an international

consortium.

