## Primary endpoint

• Changes in coronary microvessel function assessed by a transthoracic Doppler echo (TTDE) measured CFVR

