## Secondary endpoints

• Changes in symptom burden assessed by the Seattle Angina Questionnaire (SAQ)

• Changes in biomarkers including inflammatory markers and markers of metabolism

• Changes in exercise capacity (VO_2_peak)

• Changes in body weight and fat distribution (DEXA scan)

• Changes in level of anxiety and depression (HADS questionnaire)

• Changes in systolic and diastolic heart function at rest and during stress including advanced imaging (eg. Strain-Echocardiography)

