## Blinding

- Blinding of participants and investigators to treatment allocation is not possible due to the study setup.
- All baseline assessments will be conducted before randomization.
- Reading of the primary outcome CFVR and TTSDE at follow-up will be blinded.
- VO_2_max test at follow-up will be blinded to the conducting physiotherapist.
- DEXA scan at follow-up will be blinded to the conducting MD.

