# Statistics

## Sample size

The primary endpoint is change in microvascular function assessed by CFVR.

We wish to be able to detect a difference in change in CFVR between groups of 10%, equal to a change in CFVR of 0.24, assuming a baseline mean CFVR of 2.4. According to our previous study (22) the standard deviation of the within individual change is assumed to be 0.3. With power of 0.8 and two-sided significance level of 0.05, 26 patients should be included in each group. With 26 in each patient group we will be able to detect a moderate or larger effect on symptom burden. Anticipating dropout, randomization of a total of 60 patients was chosen. Dropout within the first three weeks of inclusion is replaced by new inclusion.

SAQ has four subscales each with a score from 1-100. We have not found data on within-study subject variation on SAQ. However, previous trials have obtained changes in SAQ of 10-20 points after intervention.^18^ ^46^ ^13^ A trial of 46 patients (predominantly women) with microvascular angina randomized to either ranolazine, ivabradine or placebo for four weeks found a SAQ score change of 10-40 points across different SAQ parameters, all highly significant (p<0.001).^18^ We will conduct a study on a similar study population, and we therefore expect to have the statistical power to document clinically relevant effects.

With 60 participants included, the probability is 80 percent that the study will detect a treatment difference at a two-sided 0.05 significance level, if the true difference between treatments is 11. This is based on the assumption that the standard deviation of the response variable is 15.

Analyses will be performed in STATA/IC 13.1. Categorical data will be presented as number (percentage), continuous data as mean (SD) or median (interquartile range) if normal distribution cannot be assumed. Regression analysis will be performed with the primary outcome change in symptoms (SAQ) and the independent variable change in CFVR.

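### The statistics section labels SAQ change as primary, although CFVR is the primary endpoint, and the only inferential analysis it states is not the randomised comparison

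*Protocol*

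**What the plan says.** Three places in the protocol make CFVR primary:

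- Primary endpoint: "Changes in coronary microvessel function assessed by a transthoracic Doppler echo (TTDE) measured CFVR".
- Blinding: "Reading of the primary outcome CFVR and TTSDE at follow-up will be blinded".
- Sample size, opening line: "The primary endpoint is change in microvascular function assessed by CFVR".

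The Secondary endpoints list begins with SAQ: "Changes in symptom burden assessed by the Seattle Angina Questionnaire (SAQ)."

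The Sample size section closes with the analysis plan. After one sentence on software and one on descriptive summaries, it says: "Regression analysis will be performed with the primary outcome change in symptoms (SAQ", and it takes change in CFVR as the independent variable. The protocol states no other inferential analysis.

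The sizing is framed as a comparison of arms: "We wish to be able to detect a difference in change in CFVR between groups of 10%, equal to a change in CFVR of 0.24". It assumes an SD of change of 0.3, power 0.8 and two-sided 0.05, and arrives at 26 per group, with 60 randomised to allow for dropout. A second power statement uses a difference between treatments of 11, an SD of 15 and 60 participants. It names no outcome, but it follows the SAQ paragraph and is on the SAQ scale.

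**The concern.** Within one section, two different outcomes carry the primary label. The choice between them matters. CFVR is an imaging measure read blind at follow-up. SAQ is completed by women who know whether they had the diet, training and medication programme. If the label is left open until results are known, a report could present SAQ as primary and cite the protocol for it.

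The sentence also ties the primary label to an analysis that randomisation does not protect. A regression of change in SAQ on change in CFVR asks whether women whose flow reserve rose also felt better. That is a reasonable proof-of-concept question, but it is an association between two things measured after allocation. It does not ask whether the intervention changed CFVR.

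**Working it through.** **1. The plan's CFVR figure.** Inputs from Sample size: difference 0.24 (10% of 2.4), SD of change 0.3, power 0.8, two-sided 0.05. Standardised difference = 0.24 / 0.3 = 0.8.

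- Normal approximation: n = 2 × (1.960 + 0.842)² / 0.8² = 24.5, so 25 per group.
- Two-sample t-test: 25.5, so 26 per group, as stated.
- Power by t-test: 81% at 26 per group, 86% at 30 per group.

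The sample size is therefore correct, and it is a sample size for comparing CFVR change between arms.

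**2. SAQ as primary.** I read the second power statement (difference 11, SD 15) as referring to SAQ. Standardised difference = 11 / 15 = 0.733.

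- 30 per group: 79.8% by t-test (81% by normal approximation), so the stated 80% holds if all 60 are analysed.
- 26 per group, the number the plan counts on for CFVR: 0.733 × √(26/2) = 2.64, and 2.64 − 1.96 = 0.68, giving 75% by normal approximation and 74% by t-test.

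The outcome would also be undefined. The SAQ section lists five scales and says they are not combined into a summary score, the Sample size section speaks of four, and neither selects one.

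**3. The stated regression.** No sizing is given for it. By Fisher's z, the correlation detectable with 80% power is tanh(2.802 / √(n − 3)):

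- n = 52: tanh(2.802 / 7.000) = 0.38
- n = 60: tanh(2.802 / 7.550) = 0.35

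**4. Can the regression stand in for the arm comparison?** Two illustrative cases were simulated with 30 per arm, SDs of 0.3 and 15, and 5,000 trials each. The within-arm correlations are assumptions, because the protocol gives none.

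| Case | Regression significant | CFVR, arm v arm | SAQ, arm v arm |
|---|---|---|---|
| No treatment effect, within-arm correlation 0.4 | 90% | 5% | 5% |
| True effects 0.24 and 11, within-arm correlation 0 | 16% | 86% | 80% |

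Hand checks on the regression column, with n = 60:

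- First case: atanh(0.4) × √57 = 0.424 × 7.550 = 3.20, and 3.20 − 1.96 = 1.24, so about 89%.
- Second case: the arm effects alone induce a pooled covariance of 0.24 × 11 / 4 = 0.66. The pooled variances are 0.09 + 0.24²/4 = 0.1044 and 225 + 11²/4 = 255.25. The correlation is 0.66 / √(0.1044 × 255.25) = 0.128, so power is about 16%.

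The regression can be strongly positive when the intervention does nothing, and usually negative when it works as planned on both outcomes.

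**The case against.** The strongest reply is that the word primary is a slip. The sentence sets it against an independent variable, so it may only mean the dependent variable of that regression. The regression suits the stated hypothesis that improving microvascular function relieves angina, and every other statement of the primary endpoint points to CFVR. This may well be what was meant. But the text does not say so, and the Blinding section uses the same term, primary outcome, for CFVR.

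Three stronger readings are tempting and are not supported:

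- *The randomised comparison has no test.* Sample size gives the between-group CFVR contrast, the significance level, the sidedness and the power. A statistical analysis plan may supply the model, and leaving it there would be no fault. Nothing says the regression replaces the arm comparison.
- *Success could be claimed on either outcome, so the type I error is inflated.* No section sets such a rule. The Aims section asks whether the "intervention is feasible and results in improvement in both angina and CMD". If improvement in both were required, there would be no inflation.
- *CFVR will be analysed as an unadjusted change score.* The endpoint is a change and the sizing uses the SD of change, but no model is fixed. Change regressed on arm and baseline gives the same treatment estimate as the 24-week value regressed on arm and baseline.

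**Conclusion.** The contradiction stands on the page and depends on nothing outside the protocol. SAQ change is called primary in one sentence, against three statements that CFVR is primary and a list that makes SAQ secondary. The only inferential analysis that the protocol fixes carries the wrong label and is not a comparison of randomised arms. A separate analysis plan could not settle this without departing from one of the protocol's own statements.

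The sample size is not in question. The practical cost is ambiguity about which outcome decides the trial, between a blind-read measure with 81% power at 26 per group and an unblinded self-report with no scale chosen and about 74%. The 74% rests on reading the second power statement as SAQ. The simulation percentages rest on the assumed correlations and serve only to show that the regression and the arm comparison answer different questions. The label should be corrected before any outcome data are seen.

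**What to change.** Replace the last sentence of the Sample size section with text to this effect:

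*The single primary outcome is CFVR. The primary analysis compares CFVR at 24 weeks between the randomised arms, with baseline CFVR as covariate. SAQ is a secondary outcome, and each scale is compared between arms in the same way. The association between change in SAQ and change in CFVR is examined by regression as an exploratory analysis.*

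The baseline covariate uses a scan that is already collected, so the precision it brings is free. How much it brings depends on the correlation between baseline and follow-up, which the plan does not give.

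The cost is a wording amendment, with no change to sample size, visits or measurements. How women who are withdrawn or replaced enter the analysis is a separate matter that this wording leaves open.

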Although microvessel disease is thought to be the cause of angina in a large proportion of patients, CMD is also demonstrable in asymptomatic individuals with cardiovascular risk factors. Data derived from eastern Denmark indicate that more than 50% of women with angina have CMD^4^ but comparative studies of the prevalence of CMD in asymptomatic individuals have not been performed. Thus, CMD may merely be an innocent bystander related to the presence of cardiovascular risk factors rather than the cause of angina symptoms. Furthermore, only a handful of interventional studies have simultaneously addressed CMD and symptoms in this patient group and with diverging results.^18^ ^19^ Thus there is a need of studies showing ‘proof-of-concept’, i.e. that improvement of CMD also improves angina symptoms in these patients.

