### Seattle Angina Questionnaire - SAQ

Improving quality of life is one of the primary goals in treating patients with stable angina pectoris. Quality of life is increasingly used as a patient-centered endpoint in cardiovascular disease studies, especially for stable ischemic heart disease. From a patient point of view angina may be the most important factor reducing quality of life, and data suggest that angina frequency predicts higher rates of cardiovascular events and death.^43^ Angina symptoms may not always be associated with an impaired CFVR, and conversely^44^ but interventions with ACE-I^18^ or weight loss ^45^ have improved angina symptoms (assessed by SAQ or Canadian Cardiovascular Society, CSS) and CFVR in previous studies.

The SAQ is a reliable, predictive tool that has been validated in 175 women with a confirmed diagnosis of stable coronary artery disease (CAD) and angina pectoris ^46^. It is a 19-item health-related quality-of-life measure for patients with coronary artery disease. The answers given by the patients in the SAQ’s questions are used to calculate scores in five scales:

- Anginal Stability: Whether a patient’s symptoms are changing over time.
- Anginal Frequency: Present frequency of symptoms.
- Physical Limitation: How much a patient’s condition is hampering her physical abilities.
- Treatment Satisfaction: How well a patient understands and what she thinks of it.
- Quality of Life: A measure of the overall impact of a patient’s condition on her interpersonal relationships and state of mind.

Scale scores are transformed to a 0-100 range by subtracting the lowest possible scale score, dividing by the range of the scale and multiplying by 100. Higher scores indicate less symptom burden. Because each scale monitors a unique dimension of coronary artery disease, no summary score is generated. A score change of 10 points is clinically perceptible to patients and is considered a clinically relevant difference, while a substantial change is considered to be a change of 20 points^47^ (please see Appendix for SAQ).

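### The regression of SAQ change on CFVR change names no term for randomised arm, so pooling the arms can produce a slope with no association within either arm

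*Protocol*

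**What the plan says.** The last paragraph of the protocol's Sample size section describes one model: "Regression analysis will be performed with the primary outcome change in symptoms (SAQ) and the independent variable change in CFVR". It gives one outcome and one independent variable. No section mentions randomised arm, an analysis within arms or any covariate for this regression.

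The Background explains why a link between the two changes matters. It warns that "CMD may merely be an innocent bystander related to the presence of cardiovascular risk factors rather than the cause of angina symptoms" and asks for studies showing that "improvement of CMD also improves angina symptoms in these patients".

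Three other statements bear on how the regression will behave:

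- The Methods section describes the intervention as diet, exercise training and optimised medication together.
- The Blinding section says: "Blinding of participants and investigators to treatment allocation is not possible due to the study setup". SAQ is completed by the patient.
- The SAQ section lists five scales and adds: "Because each scale monitors a unique dimension of coronary artery disease, no summary score is generated". The Sample size section counts four subscales.

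**The concern.** A successful trial will have one arm with higher CFVR change and higher SAQ change than the other. Plotted together, the two arms form two clouds with different centres, and a line through the pooled points slopes upward because of those centres alone. SAQ can rise through weight loss, fitness, attention from staff or open-label reporting, whether or not CFVR plays any part. The pooled slope would then be positive in exactly the situation the Background calls the bystander explanation.

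What is at stake is how a positive result is read. If the sentence is followed as written, a significant slope may be presented as evidence that women whose microvascular function improved had fewer symptoms, when it only restates that the intervention shifted both means. The randomised comparison of CFVR, which is the primary endpoint, is not affected.

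**Working it through.** **Planning figures reproduced first.** For CFVR the protocol uses a difference "equal to a change in CFVR of 0.24, assuming a baseline mean CFVR of 2.4", with the statement that "the standard deviation of the within individual change is assumed to be 0.3". The normal approximation gives n = 2 × (1.96 + 0.84)² × 0.3² / 0.24² ≈ 24.5, so 25 per arm. The t-test version gives 25.5, so 26 per arm, as stated. For SAQ the protocol claims 80% power with 60 women "if the true difference between treatments is 11" and the SD is 15. With 30 per arm, power is 0.81 (normal) or 0.80 (t-test). Both figures reproduce and are not in dispute.

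**Inputs to the regression check.**

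- From the Sample size section: CFVR difference dC = 0.24 with SD 0.3; SAQ difference dS = 11 with SD 15; two-sided 5% level; 26 per arm (evaluable) or 30 per arm (randomised). Cited earlier trials saw SAQ changes of 10–20 points, so dS = 20 is also run.
- Assumption: the correlation between the two changes within each arm is zero. The protocol gives no figure, and this is the scenario of interest.
- Assumption for range: an SD of CFVR change of 0.40, which the protocol does not state.

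**Expected pooled slope and correlation (1:1 arms, no association within arms).**

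- Covariance from the arm means: dC × dS / 4 = 0.24 × 11 / 4 = 0.66.
- Pooled variance of CFVR change: 0.3² + 0.24²/4 = 0.0900 + 0.0144 = 0.1044.
- Pooled variance of SAQ change: 15² + 11²/4 = 225 + 30.25 = 255.25.
- Slope = 0.66 / 0.1044 = 6.3 SAQ points per 1.0 CFVR.
- r = 0.66 / √(0.1044 × 255.25) = 0.66 / 5.16 = 0.13.

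For dS = 20: covariance 1.20, slope 1.20 / 0.1044 = 11.5, r = 1.20 / √(0.1044 × 325) = 0.21.

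**Rejection rates.** These come from 40,000 simulated trials per setting, with normal errors independent within arm.

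| SD of CFVR change | SAQ difference | No arm term, 26 / 30 per arm | With arm term |
|---|---|---|---|
| 0.3 (protocol) | 0 | 5% / 5% | 5% |
| 0.3 (protocol) | 11 | 15% / 16% | 5% |
| 0.3 (protocol) | 20 | 32% / 36% | 5% |
| 0.40 (assumed) | 11 | 11% / 12% | 5% |
| 0.40 (assumed) | 20 | 21% / 24% | 5% |

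The first row shows that the inflation needs both arm differences: with no SAQ difference the pooled test holds its level.

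**Price of the arm term.** If the true correlation within arms were 0.4 (an assumption) with the planned arm differences and 30 per arm, power is 89% with the arm term and 98% without it. Part of the 98% comes from the difference between arm means and is not evidence of a link within arms.

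**The case against.** The best defence is that one sentence in a protocol is not a closed model. It does not say the regression is unadjusted or pooled, and covariates are commonly left to a SAP, which is not available here. This stands to the extent that a SAP could add arm. But the protocol does more than stay silent: it writes out a model with a single independent variable, and that model carried out as written has the problem shown.

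The size is also modest on the planning values: a spurious correlation of 0.13 and roughly three times the nominal error rate, in a study that calls itself a pilot. That is fair, and it sets the weight of the point.

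Three stronger readings are tempting and are not supported:

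- *That this regression is the only analysis bearing on the hypothesis.* The Hypothesis and Aims sections also rest on the randomised comparisons of CFVR and SAQ, which are the primary and a secondary endpoint. Nor does the protocol state a purpose for the regression. That it is meant to tell cause from bystander is an inference from the Background.
- *That measurement error in CFVR makes a null slope uninformative.* The repeatability coefficient of 0.70 in the CFVR procedures section comes from a different, overweight population. It implies an error SD for change of 0.70 / 1.96 = 0.357, which exceeds the planned SD of 0.3 and would make reliability negative: 1 − 0.357² / 0.3² = −0.42. Any attenuation figure therefore needs an SD of change that the protocol does not give.
- *That an arm term makes the slope causal.* CFVR change is not randomised. Within the intervention arm, adherence or weight loss could drive both changes.

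**Conclusion.** The point holds for the arm term. As written, the regression can show a link between symptom change and CFVR change that exists in neither arm. On the protocol's own planning values the false-positive rate is about 15–16%, and about 32–36% if the SAQ difference reaches 20 points. It falls to 11–12% and 21–24% if CFVR change is more variable (SD 0.40, assumed).

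These figures assume that the intervention shifts both CFVR and SAQ and that the changes are independent within arms. The first condition is the outcome the trial is powered to find. The correction should be made, but it concerns the interpretation of a linking analysis and leaves the primary comparison and the sample size untouched.

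**What to change.** Restate the regression so that it includes randomised arm, baseline SAQ and baseline CFVR alongside change in CFVR. Name the SAQ scale that serves as outcome, since no summary score exists and the sentence as it stands could apply to any of the scales. State that the arm-adjusted slope will be reported as an association within arms and does not by itself show that improved microvascular function caused symptom relief.

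The cost is a longer model statement and a sentence on interpretation. The slope will be less precise and less likely to reach significance: in the example above, power falls from 98% to 89%, though part of that loss is the spurious between-arm component being removed.

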# Risks and disadvantage for participants

According to previous trials, patients with microvessel disease have an increased risk of cardiovascular mortality and morbidity. To date no approved treatment for microvessel disease exists. This study may add to the understanding of microvessel disease and possible treatment options with a direct effect on the microvasculature. By improving microvessel function the progression of cardiovascular disease may be prevented in these patients. At the individual level, participants randomized to intervention in this study will hopefully benefit from the comprehensive support and treatment team towards a more heart-healthy lifestyle and increased quality of life. By this intervention it is possible for participants to improve their physical condition, achieve fat reduction, especially the visceral fat surrounding the heart and other vital organs and thereby reduce risk factors for cardiac disease, among these hypertension, diabetes and metabolic syndrome. Risks and disadvantages are considered offset by the potential benefits of the study.

Expected disadvantages are discomfort/pain in relation to blood testing, risk of following rash or bruises that are considered harmless and will disappear after a few days.

Adenosine, which might be used during the CFVR measurements instead of dipyridamole, has known side effects similar to dipyridamole. Adenosine side effects are observed more frequently, however, they normally last for only one minute. In case of severe disadvantage for the participant in relation to infusion of adenosine an antidote, Teofyllamine, will be given. Hereafter symptoms usually diminish within minutes.

Exercise training will be monitored by a physiotherapist with experience in cardiac rehabilitation. There will be supportive health educated staff in the building in case of emergency as well as resuscitation equipment. Participating in exercise training is considered safe.

The low calorie diet with Cambridge Weight Plan has been used in studies of overweight patients without being associated with health risk.^52^ The diet intervention will be guided by a clinical dietician experienced in cardiac rehabilitation.

By Dexa scan the participant is exposed to a radiation dose of about 0.005 mSv which is considered insignificant. In comparison the annual background radiation in Denmark is

2 - 20 mSv depending on location.

